## Introduction

### The Importance of Brushing Teeth Twice a Day

Dental caries is a disease with marked socioeconomic and regional disparities. In Oregon, untreated tooth decay is twice as common in low-income children than in children from higher income families (25% vs 13%) [1]. Similarly, almost three-quarters (73%) of 6 to 9 year old children in rural Central Oregon experience tooth decay, while the statewide average is 52% [1]. Dental caries can be prevented through regular toothbrushing with fluoridated toothpaste [2-5]. The American Academy of Pediatric Dentistry and the American Dental Association recommend that toothbrushing should be performed twice daily with a fluoride toothpaste and a soft toothbrush initially by the parent, and eventually by the child [6,7]. Relatively few parents and children fully follow this recommendation [8].

Successful behavioral interventions focus on helping people acquire skills and motivation to change behavior; they are sustained and comprehensive; and, they engage peers and family members to help maintain motivation [9]. Toothbrushing beginning in infancy is a good candidate behavior. It is similar to other mildly intrusive caregiving behaviors that parents accept learning, and infants grow to tolerate. Parents’ confidence to carry out this behavior is the best predictor of being caries free at age 4 [10,11]. Once established, childhood toothbrushing habits persist [12,13], but need to be reinforced.

Toothbrushing promotion programs that provide advice, free toothpaste, and toothbrushes at a child health visit and/or by mail have shown positive effects on parents’ behaviors, including the frequency of twice daily toothbrushing of their children [14]. When accompanied by social support and in-person instruction, toothbrushing promotion programs show decreases in childhood caries and improved oral hygiene [15-17]. A program similar to that designed for the intervention study described here led to increased frequency of toothbrushing at home [17], and a 30% reduction in tooth decay [16].

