#### Data Collection

Data on type, amount, and cost of dental care will be collected through health information systems of the dental care organization (Enrollment and Claims Database) for all participants. For children less than 36 months old, information on the children’s toothbrushing behaviors, parent-rated oral health and oral health-related quality of life of the child, child’s juice consumption and frequency, parental self-efficacy, intention and attitudes regarding brushing the child’s teeth, parent educational level, and their opinions about each component of the intervention will be collected through telephone interviews with parents/caregivers at baseline and at the end of the intervention. For children less than 36 months old at baseline, information on the presence of untreated dental caries (cavitated caries in permanent or primary teeth) will be collected through a clinical examination 24 months after the study start date. Fidelity information will be obtained through examination of internal records of mailings, returned mail receipts, and telephone calls.

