### Statistical Analysis

#### Sample Size

Sample size for dental care outcomes was not calculated, as the sample size of 20,000 participants was deemed sufficient to observe an effect of the intervention on the primary outcome of restorative care utilization.

Prevalence and effect size estimates for frequency of twice daily toothbrushing among children less than 36 months old at baseline was based on that reported in a study in a similar population [25]. Assuming a proportion in the passive control group of .6, alpha = .025, beta = .20, the required sample sizes for effect sizes of 50% and 40% are 39 and 66 participants in each group. We decided on a sample size of 150 participants in each group.

Untreated dental caries estimate was based on that reported in a study in a similar population [1]. Assuming a proportion of children with dental caries experience in the passive control group of .5, alpha = .025, beta = .20, the required sample sizes for effect sizes of 30% and 40% are 206 and 113. We decided on a sample size of 210 participants in each group.

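### The caries sample size assumes a control rate of .5 for caries experience, but the examination records untreated caries, for which the article's only low-income figure is 25%, so the 80% power is not supported.

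*Protocol article*

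**What the plan says.** **Sizing (Sample Size section).** The paragraph on caries opens with its source: "Untreated dental caries estimate was based on that reported in a study in a similar population [1]". The next sentence sets the inputs: "Assuming a proportion of children with dental caries experience in the passive control group of .5, alpha = .025, beta = .20". The result is that "the required sample sizes for effect sizes of 30% and 40% are 206 and 113", and the choice made is: "We decided on a sample size of 210 participants in each group".

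**Outcome (Data Collection section).** For children under 36 months at baseline, the presence of untreated caries, defined as cavitated lesions in primary or permanent teeth, "will be collected through a clinical examination 24 months after the study start date".

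**What source 1 is quoted for (Introduction, section on the importance of brushing twice a day).** Two kinds of figure are given:
- Untreated decay: "untreated tooth decay is twice as common in low-income children than in children from higher income families (25% vs 13%) [1]".
- Decay experience: "almost three-quarters (73%) of 6 to 9 year old children in rural Central Oregon experience tooth decay, while the statewide average is 52% [1]".

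**Role of the outcome.** The Outcomes section lists dental caries among the secondary and tertiary outcomes. The Statistical Analysis Plan section makes it a secondary hypothesis, with the test and active control groups each expected to have less caries than the passive control.

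**The concern.** Caries experience counts treated as well as untreated decay, so it cannot be lower than untreated decay in the same children and is usually higher. The sizing paragraph names one quantity as its basis and puts in the other. The examination, as described, collects the one that was not put in.

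The planning rate of .5 is twice the untreated-decay figure that the article quotes from the same source for low-income children. For a fixed relative reduction, the required sample size rises steeply as the control rate falls, so the mismatch bears directly on the power claim.

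If the true control rate is well below .5, a caries comparison that finds no difference would carry little information but would read as an 80%-powered negative result. The Discussion says the evaluation will inform whether the program is sustained and expanded, so that misreading could matter.

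**Working it through.** **Inputs**
- Control rate p0 = .5, alpha = .025, beta = .20, effects of 30% and 40%, 210 per group (Sample Size section). The article does not say whether alpha is one- or two-sided, or whether the effects are relative. Both are settled by what reproduces its figures.
- Untreated decay in low-income children: 25% (Introduction).
- Age at examination: 0 to 35 completed months at baseline plus 24 months gives 24 to 59 months.
- Passive control: 150 families (Trial Status section).

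**Step 1. Reproduce the article's figures.** With p1 = p0 × (1 − effect) and p̄ the mean of p0 and p1, the pooled-variance formula is

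n = [z(α) × √(2p̄(1 − p̄)) + z(β) × √(p0(1 − p0) + p1(1 − p1))]² / (p0 − p1)²

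where z(α) = 2.2414 (two-sided .025) and z(β) = 0.8416.
- .50 vs .35: (1.5670 + 0.5816)² / 0.15² = 205.2, so 206.
- .50 vs .30: (1.5529 + 0.5708)² / 0.20² = 112.8, so 113.

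Both match exactly. A one-sided alpha of .025 would give 170 and 93. The article therefore used a two-sided .025 and relative reductions, and its arithmetic is correct.

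**Step 2. Change only the control rate, to .25.**
- .25 vs .175: (1.2967 + 0.4848)² / 0.075² = 564.3, so 565 per group.
- .25 vs .15: (1.2679 + 0.4724)² / 0.10² = 302.9, so 303 per group.

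**Step 3. Power with 210 per group.** Power = Φ{[(p0 − p1) − z(α) × s0] / s1}, where s0 is the pooled and s1 the unpooled standard error of the difference.
- 30% reduction: (0.075 − 2.2414 × 0.03992) / 0.03975 = −0.364, power 35.8%.
- 40% reduction: (0.10 − 2.2414 × 0.03904) / 0.03873 = 0.323, power 62.7%.
- At this control rate, 80% power is reached only at a relative reduction of about 47%.

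**Step 4. Range.** The documents give no rate for Central Oregon children aged 2 to 4. Apart from .25 and the article's own .5, the control rates below are assumptions.

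| Control rate | Power, 30% reduction | Power, 40% reduction |
|---|---|---|
| .15 | 20% | 36% |
| .20 | 27% | 50% |
| .25 | 36% | 63% |
| .30 | 45% | 74% |
| .35 | 54% | 83% |
| .40 | 64% | 90% |
| .50 (article) | 81% | 98% |

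To keep 80% power with 210 per group, the control rate must be at least about .49 for a 30% reduction or about .33 for 40%.

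**Step 5. Group sizes available.** The secondary hypothesis compares with the passive control, to which only 150 families were randomized. Examining 210 children there would take 210 / 150 = 1.4 children per family. With 150 passive controls against 210, power at .25 is 30.9% (30% reduction) and 55.2% (40%).

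**The case against.** The strongest reply is that .25 is not established for these children either. The Introduction gives it for low-income children in Oregon, with no age and no county. The region's decay experience is above the state's (73% against 52%). If untreated decay scaled in the same way, which is an assumption, 25% × 73/52 would be about 35%. Power would then be 54% for a 30% reduction but 83% for 40%, so the larger planned effect would keep its 80%. This stands, and it is why power should be given as a range. It does not restore the claim behind 206 and 210, because that claim rests on the 30% effect and needs a rate of about .49.

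A second reply is that the sponsor may have meant caries experience all along. The Outcomes section says only dental caries, and the Recruitment section cites a national objective on caries experience at ages 3 to 5. This also stands: reconciling in that direction is open, provided that the examination records experience and the rate is justified for ages 2 to 4.

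Three stronger readings are tempting, and the documents do not support them:
- That .5 was taken from the statewide 52% in 6 to 9 year olds. The article does not say which figure it used, and .5 could equally be the local 73% adjusted downward for younger children.
- That power simply is 36%. That is one case, conditional on a 25% control rate and the smaller of the two planned effects.
- That 206 and 113 are miscalculated. They are exact for the stated inputs.

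**Conclusion.** The point holds as a mismatch between the planning rate and the outcome examined. The sizing paragraph cites an untreated-caries estimate and uses an experience rate of .5, while the examination records untreated caries. The 80% power tied to 206 and 210 is therefore not supported for that outcome.

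On the article's only untreated-decay figure for low-income children, power with 210 per group is about 36% for a 30% reduction and 63% for 40%. It is about 31% and 55% if the passive control group supplies 150 children. These figures rest on a two-sided alpha of .025, relative reductions, independent children, no losses, and a 25% rate whose age and county are unknown.

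A reader might infer that the trial as a whole is underpowered. The documents do not support that: caries is a secondary or tertiary outcome, and the primary outcomes of restorative care and brushing frequency do not depend on this calculation. The point is worth correcting but is not essential to the primary analyses.

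**What to change.** 1. In the Sample Size and Data Collection sections, settle whether the outcome is untreated caries or caries experience, and make the planning rate match it.
2. If it stays untreated caries, base the calculation on the article's 25%, with a range labelled as an assumption, for example .15 to .40. If it becomes experience, have the examination record experience and justify the rate for ages 24 to 59 months.
3. State that alpha is two-sided and that the effects are relative reductions. Restate power for both effects at the group sizes actually available, allowing for the 150 passive control families.
4. Report the caries comparison as an estimate with a confidence interval, and do not describe it as an 80%-powered test.

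If the outcome stays untreated caries, the cost is rewording one paragraph and accepting a less favourable power statement. No additional children are needed. Changing to experience would also change what the examiners record.

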#### Recruitment

Participants will be identified through an electronic search of the enrollment database of Advantage Dental Services. All Advantage Dental Services members meeting the eligibility criteria will be included. The intervention will be delivered to all children less than 21 years old, but the evaluation of parent-reported twice daily toothbrushing and dental caries outcomes will focus on children less than 36 months old. Advantage Dental Services decided to focus on these children because of the Healthy People 2020 objective OH-1.1 to, "Reduce the proportion of children age 3 to 5 years with dental caries experience", the belief in the lifelong benefit of establishing toothbrushing habits in early childhood, and the cost implications of providing care for children this age who experience tooth decay. Because of all this, a random subsample of parents/caregivers of children less than 36 months old and a random subsample of children less than 36 months old will be recruited. Parents/caregivers of children less than 36 months old to be interviewed will be recruited through telephone calls. Children less than 36 months old to be clinically examined will be recruited at community settings such as Head Start and the Special Supplemental Nutrition Program for Women, Infants, and Children. The parents/caregivers will have the quality improvement project explained to them and have the opportunity to opt out of the evaluation.

The University of Washington Institutional Review Board reviewed this study. Consistent with US Federal regulations, participants of this quality improvement project do not meet the criteria to be considered research subjects. University of Washington personnel will have access only to deidentified data.

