### Trial Status

Participants were selected (N=21,743 families, 2857 with children less than 36 months old at baseline) and randomly assigned to the test (n=10,797), active control (n=10,796), and passive control (n=150 families with children less than 36 months old) conditions. A random sample of parents/caregivers of children less than 36 months old was interviewed (n=450, 150 for each test, active, and passive control conditions). The program has been deployed.

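### The caries examination is sized at 210 children per group, but only 150 families were randomised to passive control, so the planned size is not realistically reachable in that arm and power for the 30% effect is nearer 73% than 81%

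*Protocol article*

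**What the plan says.** The Sample Size section of the protocol article sets the inputs for the caries examination: "Assuming a proportion of children with dental caries experience in the passive control group of .5, alpha = .025, beta = .20". It then states that "the required sample sizes for effect sizes of 30% and 40% are 206 and 113" and concludes: "We decided on a sample size of 210 participants in each group".

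The Statistical Analysis Plan section makes passive control the reference for caries: the secondary hypothesis is that caries will be lower in test and in active control than in passive control. The Passive Control Condition section limits that arm to children under 36 months and their families.

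Trial Status reports randomisation as done, with 10,797 families in test, 10,796 in active control, and "passive control (n=150 families with children less than 36 months old) conditions". Of all 21,743 families, 2,857 had a child under 36 months. The Data Collection section places the examination 24 months after study start, and Results schedules it for July 2016.

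On how the children are found, the Recruitment section says that "a random subsample of children less than 36 months old will be recruited", and a little later: "Children less than 36 months old to be clinically examined will be recruited at community settings such as Head Start".

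**The concern.** The group that anchors the caries calculation is the one group too small to supply the planned number. The 150 in passive control equals the number chosen for the toothbrushing interviews, not the 210 chosen for the examination, and nothing in the article reconciles the two.

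Two things are at stake. First, the reader is led to believe that the comparison with passive control has about 80% power for a 30% reduction; a null result could then be read as stronger evidence of no effect than it is. Second, with so few passive-control families, each one not examined matters. The article does not say how the random subsample is tied to the allocation when children are reached through community settings.

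**Working it through.** **Inputs.** From Sample Size: passive-control proportion .50, alpha .025, beta .20, relative reductions of 30% (.50 to .35) and 40% (.50 to .30), and 210 per group. From Trial Status: 150 passive-control families. Sidedness is not stated, and no loss rate is given.

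**Step 1: reproduce the plan's figures.** Pooled-variance formula, two-sided alpha .025 (z = 2.2414), power .80 (z = 0.8416), no continuity correction:

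n = [2.2414 × √(2p̄(1−p̄)) + 0.8416 × √(p₁(1−p₁) + p₂(1−p₂))]² / (p₁−p₂)²

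- 30% effect, p̄ = .425: (1.5670 + 0.5816)² / .15² = 205.2, rounded up to **206**.
- 40% effect, p̄ = .40: (1.5529 + 0.5708)² / .20² = 112.8, rounded up to **113**.

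Both match. One-sided .025 gives 170 and 93, which do not. The 210 is therefore sized for the 30% effect, with 4 children per group to spare (210 − 206).

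**Step 2: families against participants.** 210 / 150 = 1.4 eligible children per family, every one examined. At one child per family the arm is 60 short (150 / 210 = 71% of plan). If 60 of the 150 families each supplied two children (90 + 2 × 60 = 210), the effective number would be about 90 + 120/(1 + ρ), where ρ is the sibling correlation. This runs from 210 at ρ = 0 to 150 at ρ = 1. The article gives no ρ and no count of eligible children per family.

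**Step 3: power with the actual arm.** With n₁ in passive control and n₂ in the comparison arm:

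power = Φ{ (|p₁−p₂| − 2.2414 × SE₀) / SE₁ }

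SE₀ uses the pooled proportion and SE₁ the separate proportions. For 150 versus 210 and .50 versus .35, the pooled proportion is .4125, SE₀ = .05263 and SE₁ = .05244. So (.15 − 2.2414 × .05263) / .05244 = 0.611, and Φ(0.611) = .729.

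| Passive vs comparison arm | 30% effect | 40% effect |
|---|---|---|
| 210 vs 210 (as planned) | 81.0% | 97.6% |
| 150 vs 210 (one child per family, no loss) | 72.9% | 94.7% |
| 120 vs 210 (assumed 20% loss in passive control) | 66.6% | 91.4% |
| 105 vs 210 (assumed 30% loss in passive control) | 62.5% | 88.9% |

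The 20% and 30% losses are assumptions chosen to show the range.

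**Step 4: can power be recovered?** Holding passive control at 150, the smallest comparison arm giving 80% for the 30% effect is 315 (power .800). Outside passive control there are 2,857 − 150 = 2,707 families with a child under 36 months, so the pool is large enough.

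**The case against.** The strongest reply is that 150 counts families while 210 counts participants, so the two need not conflict. That is formally correct. It requires 1.4 eligible children per family with complete examination at 24 months, though, and the article supports neither. The family size of 3 or 4 children in The Toothbrushing Kit section covers all ages, and correlated siblings would count for less than the independent children that the calculation assumes.

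A second reply is that the effect on the trial is limited, and this stands. The Outcomes section lists caries among the secondary and tertiary outcomes. The primary restorative-care comparison is test versus active control, with about 10,800 families each, and the brushing outcome was sized at 150 per group, which the passive arm meets. For the 40% effect, the stated requirement of 113 is below 150.

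A third reply is that a one-sided alpha of .025 would give 81.4% power at 150 versus 210. That reading does not reproduce the article's own 206 and 113.

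Several stronger readings are tempting but are not supported:

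- A reader might infer that 80% power against passive control is out of reach. It is not: enlarging the comparison arms would restore it for the 30% effect, although that is not the stated plan.
- A reader might infer that the community settings replace the allocation list and so contradict the random subsample. The article does not say so. Children could be drawn from the enrolment database and then approached at those sites, and a condensed article may leave that detail to the full protocol.
- A reader might infer that recruitment for the examination takes place two years after allocation, or differs by arm. Only the examination is dated, and nothing indicates a difference by arm.
- A reader might expect passive-control children to appear only in proportion to their share of families. The plan is for equal groups, so that scenario is not the one described.

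**Conclusion.** The caries sample size is wrong as written. A target of 210 examined children in every group does not fit a passive-control arm of 150 families, and that arm is the reference for the caries hypothesis. At one child per family, power for the effect that the 210 was chosen to detect falls by about 8 percentage points before any loss, and by about 14 to 18 points under the assumed losses. The 40% effect remains adequately powered throughout.

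These figures rest on two-sided alpha .025, which is inferred from the article's own numbers, on independent children, and on 210 examined in the comparison arm. Confidence in the numerical conflict is high. The sampling wording is at most unclear. Because a secondary or tertiary outcome is affected, at one of two stated effects, this should be corrected but does not undermine the trial's main comparisons.

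**What to change.** 1. Restate the caries sample size as at most 150 passive-control families. Give power for both stated effects, at full follow-up (73% and 95% against 210) and after the loss that the investigators expect.
2. State that the examination sample is drawn from the allocation list: all passive-control families, plus random samples of test and active-control families with a child under 36 months. Describe the community settings as places to reach and examine these children, and report the examined fraction by arm.
3. Optionally, plan about 315 children in each comparison arm, which restores 80% power for the 30% effect if all 150 passive-control families contribute a child. Any loss in passive control raises that number.
4. If more than one child per family may be examined, say so and allow for the sibling correlation.

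The cost is a less favourable power statement, an invitation list from the existing enrolment database, and some extra effort to contact listed families. The optional enlargement adds about 105 examinations per comparison arm (315 − 210). No re-randomisation is needed, and the examinations were still ahead when the article appeared in May 2015.

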### Passive Control Condition

Participants will receive the usual Advantage Dental Services practices, which may include receiving information about dental benefits via telephone and mail. This group will be on a waiting list for the trial intervention for 9 months and will then receive one toothbrushing kit. Only children less than 36 months old and their families will be included in this control condition.

By the conclusion of the study, all families will have received toothbrushing supplies. This principle, that all eligible Advantage Dental Services members will have the opportunity to benefit, is part of the organization’s mission.

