#### Statistical Analysis Plan

Descriptive statistics (means, SD, counts, and percentages) will be calculated for all variables of interest overall and stratified by age group. Difference in difference models will be used to evaluate changes in frequencies and rates for pre versus post intervention effects within the intervention groups and for passive control versus active control versus test effects. Linear regression will be used to evaluate continuous outcomes and logistic regression will be used to evaluate binary outcomes. The primary hypothesis for all participants is that the test intervention group will have a lower number of restorative dental care procedures received than the active control group during the 18 months post intervention start date. For children less than 36 months old, the primary hypothesis is that the test intervention will increase toothbrushing frequency more than the active control intervention and no change in passive control group will be observed 10 months post intervention start date. Secondary hypotheses are that member satisfaction and oral health-related quality of life of the participants will be greater and that dental care costs and dental caries will be lower in the test intervention and active control than in the passive control.

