## Results

### Timing of Recruitment, Intervention Delivery, and Follow-Up

Participants were recruited in June 2014, and the intervention is being delivered from August 2014 through April 2015. The toothbrushing supply kits were sent in August and November 2014 and February 2015. Postcards and telephone messages are being delivered to the test intervention group from August 2014 through April 2015. The helpline and other telephone services to request additional supplies are available throughout the intervention period, from August 2014 through April 2015.

Baseline interviews with the subsample of 450 parents/caregivers of children less than 3 years old have been conducted in June and July 2014, and final interviews will be conducted in May 2015. Dental claims data for all participants will be extracted in August 2015. Clinical examination of the subsample will be conducted in July 2016.

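### The caries examination is sized at 210 children per group, but its comparator arm holds only 150 families, so the stated 80% power for a 30% reduction is not supported

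*Protocol article*

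**What the plan says.** All places are in the protocol article.

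- **Sample Size** bases the caries calculation on the passive arm: "Assuming a proportion of children with dental caries experience in the passive control group of .5, alpha = .025, beta = .20". It then reports that "the required sample sizes for effect sizes of 30% and 40% are 206 and 113" and concludes "We decided on a sample size of 210 participants in each group".
- **Statistical Analysis Plan** gives the caries hypothesis among the secondary ones: "dental care costs and dental caries will be lower in the test intervention and active control than in the passive control". Both caries contrasts therefore use passive control as comparator.
- **Outcomes** lists caries among the secondary and tertiary outcomes, for children under 36 months at baseline.
- **Passive Control Condition** restricts the arm: "Only children less than 36 months old and their families will be included in this control condition".
- **Trial Status** reports the completed allocation as 10,797 test families, 10,796 active control families, and "passive control (n=150 families with children less than 36 months old) conditions".
- **Randomization and Blinding** describes equal allocation probability across the three conditions.
- **Recruitment** says the children to be examined are a random subsample found at community settings. **Data Collection** places the examination 24 months after study start, and the timetable says "Clinical examination of the subsample will be conducted in July 2016".

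**The concern.** The planned group size and the size of the randomized comparator arm do not fit together, and the arm was already fixed when the article appeared. The 150 equals the interview sample for the toothbrushing outcome. It satisfies that outcome's requirement but not the larger one set for caries.

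At stake is the stated sensitivity of the only caries outcome measured by examination; restorative care is described as a proxy. A reader of a null caries result would take it that a 30% reduction had been sought with at least 80% power. The Introduction credits a similar program with a 30% reduction in tooth decay, so this is an effect size that the article itself makes relevant.

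**Working it through.** **Inputs.** From Sample Size: passive-control proportion .5, alpha .025, beta .20, relative reductions of 30% (to .35) and 40% (to .30), 210 per group. From Trial Status: 150 passive families, and 2857 families with a child under 36 months. The article does not state sidedness; step 1 settles it.

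**1. Reproduce the plan's figures.** Pooled-variance formula, two-sided alpha .025 (z = 2.2414), power .80 (z = 0.8416), with p̄ the mean of the two proportions:

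n = [2.2414·√(2p̄(1−p̄)) + 0.8416·√(p1(1−p1) + p2(1−p2))]² / (p1−p2)²

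- .50 vs .35: (1.5670 + 0.5816)² / .15² = 205.2, rounded up to 206.
- .50 vs .30: (1.5529 + 0.5708)² / .20² = 112.8, rounded up to 113.

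Both match. The same formula gives the toothbrushing figures, 39 and 66. A one-sided .025 test would give 170 and 93, so the design basis is two-sided.

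**2. What 210 requires of the passive arm.** 210 / 150 = 1.4 examined children per family, or at least 60 siblings beyond one child per family. All must have been under 36 months at baseline and be examined two years later.

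**3. Power with fewer passive children.** Power = Φ{(|p1−p2| − 2.2414·SE0) / SE1}, with SE0 = √[p̄(1−p̄)(1/n1+1/n2)], p̄ weighted by group size, and SE1 = √[p1(1−p1)/n1 + p2(1−p2)/n2].

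For 150 vs 210 at .50 vs .35: p̄ = .4125, SE0 = .0526, SE1 = .0524, so Φ(0.611) = .729.

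| Passive vs comparison arm | 30% reduction | 40% reduction |
|---|---|---|
| 210 vs 210 (as planned) | 81.0% | 97.6% |
| 150 vs 210 | 72.9% | 94.7% |
| 120 vs 210 (assumed yield) | 66.6% | 91.4% |
| 100 vs 210 (assumed yield) | 61.0% | 87.8% |

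The lower rows assume one examined child per passive family. At 150 vs 210 the smallest relative reduction detectable with 80% power is about 32.4%.

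**4. If siblings fill the gap.** Suppose 90 single children and 60 pairs, 210 in all. The design effect is 1 + (Σm²/Σm − 1)·ICC = 1 + (330/210 − 1)·ICC. With an assumed ICC of .3 this is 1.171, the effective passive size is 179, and power for the 30% reduction is 77.5%. With ICC .5 it is 1.286, 163 and 75.2%. With no within-family correlation it would be the planned 81.0%.

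**5. Enlarging the other arms.** Against 150 passive children, 315 per comparison arm gives 80.0%. With 120 or 100 passive children, 315 gives 73.1% or 66.9%.

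**6. Allocation.** Equal probability among the 2857 families with a child under 36 months would put about 2857 / 3 = 952 in each arm, not 150 in passive control.

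**The case against.** **Families are not children.** The 150 counts families and the 210 counts participants. The article does not say how many children under 36 months the passive families have, and does not limit examination to one per family. A reader might infer that 210 is impossible, or that examining every passive child must fall short. The article does not show that. What stands is that it offers no route to 210: the examined children are a subsample from community settings, complete examination is not planned, and clustering would bring power below 80% unless within-family correlation is small.

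**The 40% effect is still covered.** This is right. Only 113 per group are needed for it, and power is 87.8% even with 100 passive children. The loss concerns the 30% reduction, the only one of the two planning effects that calls for more than 113.

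**Caries is not primary.** Also right. The restorative-care hypothesis compares test with active control, each with more than 10,000 families, and the toothbrushing outcome needs 150 per group, which passive control meets. This limits the severity.

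**Might all three examined groups be capped at 150?** A reader might take the subsample in the timetable to be the 450 interviewed families, which would give 150 vs 150 and 65% power. The article does not support relying on that: Recruitment describes the interview and examination subsamples separately, with different routes of recruitment.

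**Conclusion.** The point holds in a limited form. The planned 210 per group is not reconciled with a comparator arm of 150 families, and the 80% power for a 30% caries reduction is unsupported. With one child per family and every passive child examined against 210, power is about 73%; it is about 67% or 61% if 120 or 100 are examined. Those two yields are illustrations, since the article gives no expected yield.

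The figures keep the plan's .5, although Sample Size describes it as caries experience while Data Collection records untreated caries; a different proportion would change them. Severity is moderate: one non-primary outcome and one of two planning effects are affected.

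**What to change.** 1. Reconcile three places: the equal-probability statement in Randomization and Blinding, the 210 per group in Sample Size, and the 150 passive families in Trial Status.
2. In Sample Size, replace 210 in each group by the passive-control number that can be achieved, and say whether more than one child per family may be examined. If so, allow for clustering.
3. Restate power for a 30% reduction as at most about 73% with one child per family. Alternatively, give the detectable reduction at 80% power as about 32% (150 vs 210). Both are before loss, so add the figure at the expected examination yield.

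The cost is a wording change and a less favourable stated power.

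Optionally, examine about 315 children in each of the test and active arms. That makes 150 + 315 + 315 = 780 examinations against the planned 3 × 210 = 630, or 150 more. If the remaining eligible families split evenly, about (2857 − 150) / 2 = 1,353 per arm are available. This restores 80% only if all 150 passive children are examined, and the text should say so.
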